#### Day 7: Follow up

Study participants will be actively followed-up by the study team (control arm, RDT-DA arm and e-Algorithm arm) on day 7 to assess their health status as well as find out if they procured other treatment different to those prescribed at the health facilities. If the participants do not come back for the control at day 7, a home visit will be performed by study staff to collect the information. For that, an additional 2 days will be given to collect this information. The caregivers will also be interviewed by social scientists the day of their follow-up (day 7) either at the health facility or at a place indicated by the caregiver if he feels this place will be better for him to freely express himself. In both cases, the place should meet the requirements for confidentiality and patients’ protection.

#### Unscheduled visits before day 7

All patients will be asked to visit the health facility at any time if the child health status is not improving or in case or worsening. This will be documented as unscheduled visit and reported in the CRF.

### Criteria for discontinuing or modifying allocated interventions {11b}

It is hypothesized that the proposed algorithm will reduce inappropriate prescription of antibiotics and antimalarials in intervention arms. However, an efficient follow-up system will be putted in place to ensure the reporting and management of adverse events requiring medical care on time. In case of frequent occurrence of related serious adverse events, the intervention will be interrupted.

### Strategies to improve adherence to interventions {11c}

The proposed tests are available on the market but are not part of the routine health system at primary health facilities. Prior to the implementation of the intervention, an explorative research will be conducted in the study area to investigate the factors that may impact on the acceptability and feasibility of implementing the intervention (introduction of new POC tests) in the routine health system, mainly among health care workers and parents/guardians. This explorative research will be conducted by a trained social science team. The outcomes of this explorative research will serve to train study staff to adopt good attitude with study participants and encourage them to adhere to study conditions during the follow-up visit.

Each participant, regardless of his randomized arm, will be follow-up at the day 7 (± 2) at the health facility to assess the health status of the child and the adherence of the parent/guardian to the prescription. The adhesion to the prescription will be assessed through a qualitative in-depth interview of parent/guardian and pill count (parents/guardians will be asked to bring back packaging and remaining medicine on day 7 visit), including behavior of parent/guardian who will not receive prescription of medication to find out if they purchased any antibiotic or any other treatment, the place of purchasing, and the reasons.

Participants who do not return at the health facilities at day 7 will be followed-up at home or by telephone to assess their wellbeing and the need to return at the health facilities.

### Relevant concomitant care permitted or prohibited during the trial {11d}

Parents/guardians will be asked to return at the recruitment site with the participants if the symptoms persist and/or health conditions worsening. However, participation in the study is voluntary and parents are free to judge the need for concomitant care for their children. Nevertheless, parents/guardians will be asked to report any concomitant care to the study staff. No routine interventions are prohibited during the trial.

### Provisions for post-trial care {30}

Given the fact that this is a diagnostic trial and not an interventional clinical trial testing a new drug/device, such visits are not needed.

### Outcomes {12}

Primary study outcomes will be:(i)The rate of febrile cases with favorable outcomes at day 7 in each arm;(ii)The proportion of antimalarial and antibiotic prescriptions for acute febrile at the health facilities in each arm at day 0.

Secondary outcomes include:(i)The adherence of healthcare workers to the algorithm at day 0;(ii)The adherence of parents/guardian to treatment. This will be assessed at day 7 visit;(iii)Accuracy of the algorithm for the diagnosis of malaria and others PoC tests to guide bacterial infections (biomarkers and pathogen-specific PoC tests). This will be assessed at day 7;(iv)The safety of the algorithm for the management of febrile diseases. This will be assessed at day 7 visit.

### Participant timeline {13}

The algorithm implementation will be based on clinical evidence that the healthcare workers will record and the test results. Study participants (children) will be identified during their visit at the health facilities. Children attending the health facilities and fulfilling the inclusion criteria will be included in this study only if their parents/legal guardian signs the informed consent forms. After signature, children will be randomized to be allocated to either in control, RDT-DA algorithm or e-algorithm arms. After the initiation of the treatment, the health outcome will be assessed at day 7. Parents will be asked to come back to the health facilities with his/her child before day 7 visit if his/her health condition is not improving or is getting worse. Study will be ended for a child if at day 7 visit clinical signs and symptoms are no longer presents; otherwise, he will be referred to the study clinician or pediatrician for better care (Table 5).

**Table 5 Tab5:**
[figure not shown]
Study flow chart

### Sample size {14}

Sample size is calculated based on data collected in the Siglé and Pella health facilities’ consultation books. From these data collected in 2018 (January to December), the proportion of febrile children under 5 years presenting at the health facilities with febrile illnesses and who were prescribed antibiotic was 62.63%. The implementation of the algorithm is expected to reduce this proportion to at least 20%. In this study, the sample size is computed to a Bonferroni correction of alpha which is performed for multiple comparisons; therefore, an alpha level of 0.017 is chosen. Type II error was controlled at 20%, i.e., (*β* = 0.20 or 80% power). Based on these parameters, a sample size of 356 is required per arm. Hence, an overall sample size for the study is estimated at 1068 (3 × 356). Further assuming that 10% of the individuals will be lost to follow-up, an adjusted sample size of 392 children per arm is required. The final estimated sample size for this study is thus 1176 children.

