### Trial design {8}

This study will be an open-label, superiority, three-arm individual randomized controlled diagnostic trial to evaluate a new algorithm including two-step malaria RDT and PoC tests for bacterial infections: (1) control arm, (2) RDT decisional algorithm (RDT-DA) arm, and (3) e-algorithm arm.

In the 3 arms, healthcare workers will be trained to perform properly the clinical examination.In the control arm, the diagnostic and management will be based on IMCI and guidelines of diagnostic and treatment (GDT). The management of the participant will be only supported by a one-step malaria RDT, rolled-out by the MoH for malaria management in primary health facilities. The diagnosis and prescription will be left to the discretion of the healthcare workers, based on the Integrated Management of Childhood Illnesses (IMCI) and GDT.In the RDT-DA arm, the presumptive diagnostic will base on IMCI and guidelines of diagnostic and treatment (GDT). This presumptive diagnostic will be supported by biomarkers PoC diagnostic tools (CRP, WBC and urine dipstick), pathogen-specific antigen RDT (two step malaria RDT and bacteria), and pulse oximetry to determine if a prescription of antibiotic is needed. However, in this arm, the diagnosis and prescription will be left to the discretion of the healthcare workers, based on clinical examination and PoC test results.In the e-Algorithm arm, the clinical examination will be supported by the two-step malaria RDT and the PoC tests for bacterial infections to determine if a prescription of antibiotic is needed. However, in this arm, the clinical evidence and the results of malaria two-step RDT and the PoC tests for bacterial infections will be digitalized to guide diagnostic and propose treatment. After the properly completion of the e-Algorithm, the final diagnosis will be done by the algorithm as well as the prescriptions (antibiotics and antimalarials mainly).

In the decisional algorithm arms (RDT-DA) and e-Algorithm arms, the PoC tests will be done by trained nurses.

In the 3 arms, the study CRFs (case report forms) of data collection will be digitalized on tablets for an electronic data collection.

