### Enrolment

#### Day 0: Screening visit/ sample collection

Informed consent: After an in-depth discussion with the study physician or a member of the study team, the parent/legal guardian of the potential participant will be asked to document his consent by signing an informed consent form. The signed informed consent form (or thumb-print whenever the patient or the parents/guardians are illiterate) must be obtained before any data or sample collection for the study is done. Patients/guardians who will not consent to let his/her child to be part of the study will receive the standard of care as recommended by the Ministry of Health of Burkina Faso.Randomization of study participants: Study participants will be randomized to routine, RDT-DA or e-Algorithm arm at a ratio of 1:1:1 using varying block size of 20, 30, or 40 subjects in random order. Randomization list will be prepared by the data management and (bio) statistic department of CRUN.Randomization of study participants into the three arms will be performed by a trained study staff, after checking the inclusion and exclusion criteria.Demographic data and medical history: Demographic data and a general medical history of past and present illnesses, including the intake of any medication in the past month, will be recorded to determine the characteristics of the study participants.Control and intervention armsControl arm:

In the control arm, participants will follow the routine standard of care for the management of febrile diseases according to the national guidelines. In this arm, HRP2 based malaria RDT will be the only diagnostic tool available for the management of the fever episode. The clinical assessment (history of presenting complaints and physical examination) will be performed by health facilities staff (nurses). Except malaria for which an RDT is available, the other prescriptions in this arm will be based on clinical signs and symptoms as defined in IMCI.RDT-DA arm

The clinical assessment of the participant (history of presenting complaints and physical examination) will be performed by the study nurses. In this arm, participants will benefit the two-step malaria RDT detecting *Pf*HRP2/*p*LDH for the diagnosis of malaria infection and PoC tests for the diagnostic of bacterial infections. Samples tested will be sent to the microbiology laboratory of CRUN for culture.

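### The stated target effect on antibiotic prescribing does not give 356 per arm: with the stated 62.63%, none of the three readings of the 20% reproduces it

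*Protocol article*

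**What the plan says.** All the inputs are in the protocol article, Sample size {14}. From 2018 consultation books at the two facilities, the proportion of febrile children under 5 years "who were prescribed antibiotic was 62.63" per cent. The target follows: "The implementation of the algorithm is expected to reduce this proportion to at least 20" per cent. For the error rates, a Bonferroni correction is applied, "therefore, an alpha level of 0.017 is chosen", and "Type II error was controlled at 20" per cent, that is, 80% power. The section then concludes: "Based on these parameters, a sample size of 356 is required per arm".

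Two other sections bear on the calculation. Trial design {8} calls the trial a superiority trial, and the Day 0 screening section fixes equal allocation: "Study participants will be randomized to routine, RDT-DA or e-Algorithm arm at a ratio of 1:1:1". Sidedness, formula and any rounding of the rates are not given. The article prints no intervention-arm proportion other than 20%.

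**The concern.** A drop from 62.63% to 20% is a difference of 42.63 percentage points. A difference that large needs a few dozen children per arm, not several hundred, so either the printed effect or the printed sample size must be something other than it seems.

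Antibiotic prescribing is part of the second primary outcome, and this is the only effect size in the article. If it is misprinted, readers cannot verify the calculation. They also cannot tell which reduction the sponsor regarded as worth detecting, so that benchmark could be reinterpreted once results are known.

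**Working it through.** **Inputs.** Control rate p1 = 0.6263; alpha = 0.017; power = 0.80; allocation 1:1 for each pairwise comparison. All are stated. A two-sided test is my assumption.

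**Formula** (two proportions, pooled variance under the null), with p̄ = (p1 + p2)/2:

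n per arm = [ z(1−α/2)·√(2p̄(1−p̄)) + z(0.80)·√(p1(1−p1) + p2(1−p2)) ]² / (p1 − p2)²

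Here z(1−0.0085) = 2.3867 and z(0.80) = 0.8416. The continuity-corrected size is (n/4)·[1 + √(1 + 4/(n·|p1−p2|))]².

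**Attempt to reproduce 356 with the stated 62.63%.**

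- Fall *to* 20% (p2 = 0.20, difference 0.4263): (1.6620 + 0.5283)² / 0.4263² = 4.7975 / 0.1817 = 26.4.
- Fall *by* 20 points (p2 = 0.4263): (1.6853 + 0.5823)² / 0.20² = 5.1419 / 0.04 = 128.5.
- Fall by 20% *relative* (p2 = 0.8 × 0.6263 = 0.50104, difference 0.12526): (1.6739 + 0.5855)² / 0.12526² = 5.1052 / 0.01569 = 325.4.

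| Reading of the 20% | p2 | n per arm | with continuity correction | power at 356 per arm |
|---|---|---|---|---|
| to 20% | 0.20 | 27 | 31 | about 100% |
| by 20 points | 0.4263 | 129 | 139 | 99.9% |
| by 20% relative | 0.50104 | 326 | 342 | 83.9% |

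None gives 356. As printed, the target needs about one-thirteenth of the stated number (356/27 = 13.2). The nearest reading, the relative one, is 8.4% short without continuity correction and 3.9% short with it. A one-sided test moves further away: the relative reading falls to 274. An unpooled variance gives 322 for the relative reading, and alpha = 0.05/3 gives 327, so neither closes the gap.

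**What 356 does correspond to.**

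- 62% to 50%, alpha 0.017: 5.1164 / 0.12² = 355.3, so 356. This is a 12-point fall, or 0.12/0.62 = 19.4% relative.
- 62.63% to 50.63%, alpha 0.017: 5.0998 / 0.12² = 354.2, so 355. With alpha = 0.05/3 it is 355.8, so 356.
- Solving for the detectable difference from 62.63% at 356 per arm, alpha 0.017 and 80% power gives p2 = 0.5066, a fall of 0.1197, or 19.1% relative.

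The number therefore corresponds to a fall of about 12 points, and more than one pair of rates leads to it.

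**The case against.** The best defence is that this is a slip of wording over a sound calculation: the authors meant a reduction *by* about 20% in relative terms and worked with whole-percent rates. Taking 62% to 50% at the stated alpha and power gives 356 on the nose. That has force, and it rules out saying that no interpretation at all can recover the figure. It does not rescue the printed sentence. Neither 62% nor 50% appears there as a rate, and 62.63% rounds to 63%, from which a 20% relative fall (to 50.4%) needs 321, or 337 with continuity correction. An exact 20% relative fall from 62% is to 49.6%, which needs 333 (349).

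A reader might go further and infer that the trial was really designed around a 12-point fall to about 51%. The documents do not support that. No 12-point effect is mentioned anywhere; it is obtained only by solving backwards from 356, and the solution is not unique. From 62.63%, it also reaches 356 only by replacing the stated 0.017 with 0.05/3.

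A reader might also infer that the trial is the wrong size, or that a significant result would be judged a failure for missing 20%. Neither follows. Every reading of the 20% needs fewer than 356 per arm, and the statistical methods section describes a comparison of proportions between arms with no 20% success threshold.

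Finally, condensing a full protocol into an article explains omissions. Here the inputs and the result are both printed, and they disagree.

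**Conclusion.** The point holds as an internal contradiction in Sample size {14}: the printed target effect and the printed sample size cannot both be right at the stated 62.63%, alpha and power. The gap is roughly thirteenfold on the literal reading and 4% to 8% on the closest one. The article does not reveal which effect was used; an undisclosed rounding combined with a *to*/*by* slip is plausible but unconfirmed.

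The harm is limited to an unclear target and a calculation that cannot be reproduced. Power for antibiotic prescribing is about 84% or more under every reading of the 20%. These figures assume a two-sided comparison of two proportions with equal arms and 356 evaluable children in each.

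**What to change.** Replace the target in Sample size {14} with the intervention-arm proportion actually entered in the calculation, taken from the sponsor's calculation file, and say whether the reduction is absolute or relative. State the sidedness, the formula and any rounding of the rates.

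If a 20% relative reduction was intended, write 62.63% to 50.1% and restate the power at 356 per arm as about 84%. In either case, add that 356 per arm detects a difference of about 12 percentage points with 80% power. A 12-point fall should not be entered as the planned effect unless the file shows that it was.

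The cost is a check of the calculation file and a sentence or two of text, carried into the analysis plan if it repeats the calculation. Enrolment does not change.

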### Recruitment {15}

Two health facilities have been selected to be part of this study based on the consultation of this age group at these health facilities to be sure to reach the sample size on time: Siglé and Pella. A monthly target enrolment plan which covers the whole year recruitment will be developed based on the monthly attendance at each health facility before the enrolment of the first participant. This target enrolment plan will be followed by the study team to be sure that the sample size will be reached on time and make some adjustment if needed (Table 1).

### Assignment of interventions: allocation

#### Sequence generation {16a}

This will be an open-label randomized controlled trial with three arms, enrolling febrile children from 6 to 59 months. A computer-generated randomization list will be prepared and generated by the data management department of CRUN. Only the central data management team will have access to the randomization list.

#### Concealment mechanism {16b}

Each randomization number and corresponding group (e-Algorithm, decisional algorithm and routine) will be sealed in an opaque envelope which will only be opened by study staff after enrolment of the participant.

#### Implementation {16c}

The central data management team of IRSS-DRCO will generate the allocation sequence. Participants will be enrolled by nurses who will assign participants to interventions (e-Algorithm, decisional algorithm arms) after confirmation of all eligibility criteria.

### Assignment of interventions: blinding

#### Who will be blinded {17a}

This is an open-label trial. Therefore, this is not applicable to this study. Nevertheless, during data analysis, data analysts will not have access to the identity of the participants or any information that can link participant to the data. The finding will be reported in summary form.

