The implementation of the algorithm will be based on the implementation of PoC tests to support clinical diagnostic and guide treatments. Study participants (children) will be identified during their visit at the study health facilities. Children attending the health facilities and fulfilling the inclusion criteria will be included in the study only if their parents/legal guardian signs an informed consent form. Upon the inclusion, children will be randomized to be allocated either in the control, RDT-DA algorithm, or e-algorithm arms. After the initiation of the treatment, the health outcome will be assessed at day 7. Those who will not return to the health facilities for day 7 visit will be visited at home by a field worker to collect the information. Patients will be asked to come back to the health facilities before day 7 if their health condition is not improving or is getting worse. Study will be ended for the child if at day 7 visit, clinical signs, and symptoms are no longer presents; otherwise, the participant will be referred to the study clinician or pediatrician for better care.

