However, in this arm, the diagnosis and prescription will be left to the discretion of the healthcare workers, based on clinical examination and PoC test results and basing Fig. 1 and Tables 2, 3, and 4.e-Algorithm arm

The clinical assessment of the participant (history of presenting complaints and physical examination) will be performed by the study nurses. In this arm, participants will benefit the two-step malaria RDT detecting *Pf*HRP2/*p*LDH for the diagnosis of malaria infection and PoC tests for the diagnostic of bacterial infections. Samples tested will be sent to the microbiology laboratory of CRUN for culture.

However, in this arm, the clinical evidence and the results of malaria two-step RDT and the PoC tests for bacterial infections will be digitalized to guide diagnostic and propose treatment. After the properly completion of the e-Algorithm, the final diagnosis will be done by the algorithm as well the prescriptions (antibiotics and antimalarials mainly).

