### Statistical methods

#### Statistical methods for primary and secondary outcomes {20a}

An analysis plan of the data has been developed and validated by the participants of the first workshop of the project, prior to the recruitment of the first study participants. Briefly, statistical analysis will be presented by treatment group. Categorical variables will be summarized as proportion, and chi-square test or Fisher’s exact test will be performed. For continuous variables, they will be described by mean or median and compared by using Student’s *t*-test. The proportion of patients that meet the criteria of the primary outcome (proportion of recovered case and antimicrobial) will be presented by arm. This analysis plan could be revised according to events and in case of amendment of the protocol. The statistical analysis will be done with an appropriate data analysis software (STATA 14.1. and R).

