#### Phase 2: Evaluation research

This research will occur during the study implementation. The aim of this investigation will be to analyze the adherence of health care workers and the community to the new algorithm. The participants will be interviewed on day 7 when they will come for the follow-up. This will help minimize forgetfulness.

*Study population*: The study population will be the healthcare workers who implemented the study in the different sites and the parents/guardians.

*Sampling and sample size estimation*: The healthcare workers who will participate in the study are those who implemented the study on the site (six nurses are expected for the two sites) and the parents/legal guardians of the study participants attending the recruitment sites (participants will be interviewed until the saturation of content is reached).

*Data collection tools*: Data (in-depth interview) will be audio-recorded under the consent of the participants.

*Data analysis*: Data collected will be transcribed manually. NVivo software will be used for the management and the coding of data. During the analysis, key topics and concepts generated will be categorized.

*Outcome of the investigation*:Primary outcome: Analyze the adherence of parents/guardians and health care workers to the algorithm.

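### Blinding is set aside as not applicable because treatment is open, which leaves the day-7 recovery and safety outcomes without any masking of the assessor; removing identities from the data does not hide the arm.

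*Protocol article*

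**What the plan says.** Who will be blinded {17a} opens with "This is an open-label trial. Therefore, this is not applicable to this study". The one measure it then offers is that "data analysts will not have access to the identity of the participants or any information that can link participant to the data".

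The first primary outcome in Outcomes {12} is "The rate of febrile cases with favorable outcomes at day 7 in each arm". That section does not define favorable. Trial design {8} shows what the visit turns on: "Study will be ended for the child if at day 7 visit, clinical signs, and symptoms are no longer presents". Participant timeline {13} repeats this rule, and the statistical methods section {20a} calls the primary outcome "proportion of recovered case and antimicrobial". Safety of the algorithm is a secondary outcome, also assessed at day 7.

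On who does the visit, Day 7: Follow up says "Study participants will be actively followed-up by the study team", and it names all three arms. On day 0, the clinical assessment in both algorithm arms "will be performed by the study nurses", while control children are assessed by the health facility's own nurses.

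**The concern.** Open treatment means that caregivers and treating nurses know the arm. It does not follow that the person who scores the outcome, or the person who analyses it, must know it too. Section {17a} runs these together, then puts a confidentiality measure where masking would normally be described. An analyst with no names in the data set can still see the arm.

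The outcome exposed is a primary one. Whether a young child's signs and symptoms have gone is partly a matter of judgement, and an assessor who knows how the child was managed may judge borderline cases differently by arm. The trial asks whether prescribing can be reduced without clinical loss, so an arm-dependent error in recording recovery bears directly on that question. The cure rate is also the effectiveness measure in the cost-effectiveness ratio (Methodology of the health economic survey), so an error there would carry through.

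**Working it through.** The article gives no figure to reproduce, so the main check is textual. A short calculation follows for scale only.

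**Text check: does any section mask the day-7 assessor or the analyst to arm?**

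- *Sequence generation {16a} and Concealment mechanism {16b}.* List access is restricted, and study staff open opaque envelopes after enrolment. This guards against selection at entry, not against biased outcome assessment.
- *Implementation {16c}.* Nurses enrol and assign, so they know the arm.
- *Day 0.* Study nurses assess the two algorithm arms; facility nurses assess control.
- *Day 7.* The study team sees all arms. Non-returners are seen at home by study staff (Day 7: Follow up) or by a field worker (Trial design {8}), or are followed up at home or by telephone (Strategies to improve adherence {11c}). No section separates these people from those who managed the child.
- *Visit content.* The same visit includes pill count, adherence questions and an interview, with no stated order relative to the assessment of health status.
- *Data capture {18a}, {19}.* A standard case report form is digitalised for each arm. No section describes the day-7 form or says that it hides the arm.
- *Analysis {20a}.* Results are presented by treatment group; arm coding is not mentioned.

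No section supplies the masking that {17a} sets aside.

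**Illustration of scale**

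Inputs: n = 356 per arm and two-sided alpha 0.017, both from Sample size {14}, where they were set for prescription. The article gives no day-7 recovery rate, so true recovery p of 80%, 90% and 95% is assumed, equal in both arms.

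Step 1, the assumed shift. Suppose 10% of children have residual signs, and an aware assessor scores 10% to 30% of them as recovered in one arm only. The shift is then

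0.10 × 0.10 = 0.01 to 0.10 × 0.30 = 0.03, that is 1 to 3 points.

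Step 2, the chance of a significant difference favouring the inflated arm when there is no true effect:

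Φ[(d − z·s0) / s1], where z = 2.387, s0 = √[2·p̄(1 − p̄)/n], s1 = √{[p(1 − p) + (p + d)(1 − p − d)]/n} and p̄ = p + d/2.

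For p = 0.90 and d = 0.03: p̄ = 0.915, s0 = 0.02090, s1 = 0.02087. Then (0.03 − 2.387 × 0.02090)/0.02087 = −0.953, and Φ = 17.0%.

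| Shift d | p = 80% | p = 90% | p = 95% |
|---|---|---|---|
| 1 point | 2.0% | 2.7% | 4.1% |
| 2 points | 4.4% | 7.3% | 15.2% |
| 3 points | 8.7% | 17.0% | 41.7% |

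With no shift the chance in that direction is 0.017/2 = 0.85%.

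The columns do not ask the same of the assessor. At 95% recovery, 3 points means rescoring 0.03/0.05 = 60% of residual cases, which is a strong assumption. At 80% it means 0.03/0.20 = 15%. A shift the other way would count against the algorithm arms.

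**The case against.** The strongest reply is that much of the alarming version is inferred.

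- *Same nurse at both visits.* A reader might conclude that the nurses who treated the algorithm arms score their own patients. The article does not say so. The study team also includes a study physician and field workers. The statement that "six nurses are expected for the two sites" describes whom the social scientists expect to interview; it is not a day-7 roster. What stands is that nothing prevents the overlap.
- *The form reveals the arm.* A reader might infer this from forms being digitalised for each arm. That sentence follows one on history, examination and prescription, which are mainly day-0 content. The day-7 form is not described, so this is a possibility only.
- *Bias favours the algorithms.* It might. But an assessor who knows that an antibiotic was withheld could equally look harder for residual illness. The article supports neither direction.
- *The outcome is subjective.* Favorable is not defined where it is listed. Fever is defined by axillary temperature in the eligibility criteria, so a measured component is plausible. The sign-and-symptom reading is a fair inference from {8}, {13} and {20a}, but it is still an inference.
- *The trial as a whole is compromised.* This does not follow. The sample size rests on antibiotic prescription, a recorded day-0 act that day-7 assessment does not touch.
- *Masking cannot work here.* Caregivers know what happened on day 0 and may disclose it, and masking the assessor does not remove bias in their own reports. This limits the benefit without making the attempt pointless.
- *Detail left to the analysis plan.* This is a fair reply for coded arm labels, which are therefore secondary. It does not answer the assessor point, because {17a} does not leave the matter open: it declares blinding not applicable.

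**Conclusion.** The point holds in a limited form. Section {17a} draws a wrong inference from open-label treatment, and its only safeguard masks no one to arm. As written, the plan allows an arm-aware person to score the day-7 primary outcome and the day-7 safety outcome.

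The size and direction of any resulting bias cannot be derived from the article. If a one-sided shift of 1 to 3 points occurred, and if true recovery were about 90%, the chance of a false significant advantage would be 2.7% to 17.0% instead of 0.85%. Both conditions are assumptions. The conclusion does not extend to day-0 prescription. This should be corrected because the remedy is cheap and a primary outcome is exposed; it does not invalidate the design.

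**What to change.** Replace the text of {17a} with a statement by role:

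1. Caregivers and treating nurses are unmasked.
2. Day-7 status, at the facility or elsewhere, is scored by an existing team member who did not manage that child on day 0.
3. One common day-7 form serves all arms and shows neither arm nor day-0 prescription. Temperature, symptom checklist and outcome are entered and locked before pill count, adherence questions and interview.
4. Any unmasking of the assessor is recorded.
5. Optionally, analysts work with coded arm labels until the primary analyses are final.

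Keep the de-identification sentence, but as a confidentiality measure.

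The cost is rostering, form configuration and a fixed visit order. The plan should confirm that whoever scores at home visits can assess clinical signs, since the article describes field workers only as collecting information. Masking will be partial because caregivers may reveal the arm.
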